### Implementation {16c}

An external person who has no other connection to the project will generate the randomization sequence and allocate a study arm to each kindergarten using a pre-fixed list of the kindergartens.

## Assignment of interventions: blinding

### Who will be blinded {17a}

N/a: This is an open-label trial.

### Procedure for unblinding if needed {17b}

N/a. This is an open-label trial.

## Data collection and management

### Plans for assessment and collection of outcomes {18a}

Data from the study will solely be collected by online digital questionnaires completed by teachers and parents via PC, tablet, or smartphone. The questionnaires are built on the EasyTrial platform [13] and will be distributed and collected by the study coordinator at Research Unit for Health Surveys [14]. Questionnaires are distributed by SMS (parents) or work e-mail (teachers) where a personal link to the questionnaire is attached. The answers are directly transferred to the EasyTrial platform.

All kindergarten teachers will be informed about the complementing procedures, and every questionnaire will contain instructions for users. Teachers in the intervention kindergartens are trained in the DBED procedure by a training session involving practical role-play.

The following questionnaires are used:

Baseline information (demographics, social support, health related information)◦ Parent’s educational level (values 0–3)◦ Satisfaction with economic situation (Visual analogue scale, values 0–10)◦ Social support, adapted from the PIRM study [15] containing nine items. See Additional file 2 for details.◦ Single parenting (values 0–1)◦ Close relatives in the vicinity (values 0–1)◦ Norwegian language at home? (values 0–1)◦ Is Norway parent’s country of origin? (values 0–1)◦ Major illness or handicap (child) (values 0–1)EWQ (only for the intervention group) [10] is a novel tool for assessing parents and kindergarten teachers’ possible concerns for a child. The psychometric properties of EWQ are not yet established but will be subject to analyses in the present study. We will apply the total EWQ score (values 0–74) and EWQ sub-scores (five sub-scores, values from 0–10 to 0–18). EWQ will be scored in two different situations:◦ Prior to the parent-teacher conference, completed by both each parent and teacher.◦ As conclusions after the parent-teacher conference, completed by teacherSDQ, 2–4 years version [16] is a standard screening tool for mental health symptoms among young children with well-established validity [16] and psychometric properties [17]. We will apply SDQ Total Difficulties Scale score (values 0–40), each sub-scale score (values 0–10), and two SDQ impact scores (values 0–3 and 0–12, respectively) addressing difficulties in general and in four different areas of daily functioning.PSS is an 18-item questionnaire (values 0–72) assessing parents’ feelings about their parenting role, exploring both positive aspects (e.g., emotional benefits, personal development) and negative aspects of parenthood (e.g., demands on resources, feelings of stress) [12].User satisfaction with the DBED method (only for the intervention group) measured after all parent-teacher conferences by study-specific questionnaires, see Additional file 2.◦ Parent questionnaire: five items (values 0–15) and optional free text response◦ Teacher questionnaire: seven items (values 0–21) and optional free text responsePossible supportive actions initiated, see Additional file 2.How specific questionnaires relate to the primary, secondary, and process outcomes, respectively, is described in the “Outcomes {12}” section. Collection of qualitative data for process outcomes is described in the “Data management {19}” section.

### Plans to promote participant retention and complete follow-up {18b}

Participation in the trial means biannual completion of online questionnaires and attending parent-teacher conferences (intervention kindergartens by DBED, control kindergartens by TAU). Participants in the intervention kindergartens will receive EWQ and invitations to DBED parent-teacher conferences by the study coordinator and kindergarten teacher, respectively, and will be given reminders when necessary. Participants in the control kindergartens will be invited to TAU parent-teacher conferences by their kindergarten teacher. The study manager and study coordinator will have regular contact with every kindergarten manager and participating teacher for continued consciousness and compliance with the study.

### Data management {19}

All data will be entered digitally by the participants themselves through questionnaires in the EasyTrial platform [13]. EasyTrial has built-in data entry validations such as range checks, data type checks, logic checks, and conditional logic checks to promote data quality. Blocks of raw data will periodically be exported by the study coordinator as SPSS files to a secure research server controlled by Helse Vest IKT. To preserve the integrity and validity of the self-reported data, a statistician will organize the data for further analysis (recode variables, compute sum scores, merge different measurements, make long/wide format files to match the analyses, aggregate and disaggregate scores within subjects) and remove missing data. The database will also be exported in full at the end of the study after database lock.

Audio recordings of parent-teacher conferences and subsequent interviews of parents and teachers (see the "Methods for additional analyses{20b}" section) will be collected by a hand-held digital recorder. A researcher will personally collect the recorders in the kindergarten, and speech from the recordings will be transcribed to text using Whisper artificial intelligence software in a PC without an internet connection. All names mentioned in the conversations are automatically changed to another name, and all dialect is changed to the default Norwegian Bokmål language. In this way, it should not be possible for the researcher to recognize who has participated in the conversation.

### Confidentiality {27}

Before consenting to participate in the study, interested parents of eligible children will provide personal contact information through the online questionnaire system. If the parents do not consent within 30 days, this information is deleted automatically. By consent, this information and further personal information of the parents and their child will be stored together with the rest of the collected data. After being removed from the data files, name and national identity number will be linked to unique ID numbers found in the main data files and stored in a separate key file. Only the study manager and study coordinator will have access to the key file. After project closure (year 2040) all data will be stored for five more years for control purposes.

### Plans for collection, laboratory evaluation, and storage of biological specimens for genetic or molecular analysis in this trial/future use {33}

N/a.

## Statistical methods

### Statistical methods for primary and secondary outcomes {20a}

Primary outcome:◦ Possible differences between children in intervention and control kindergartens in mental health trajectories will be estimated by Latent growth curve (LGC) models (gives equal results as linear mixed/multilevel models, given similar parameter specification). Both random intercept fixed slope and random intercept random slope will be analyzed, meaning models with no variance in change (slope) and models with individual differences in slope (random effects). Then the full unstructured matrix with random intercept, random slope, and the covariance between intercept and slope will be tested. Initially, linear change over time will be tested. If not supported with data, different non-linear change models will be explored (quadratic, cubic, piecewise growth). Then, substantial predictors will be entered into the model and analyzed. Also, within level residual structures will be tested.Secondary outcomes:◦ Possible differences between children in intervention and control kindergartens in parental stress and time to initiated locally available supportive action, respectively, will be analyzed in a similar way to the primary outcome.Process measures:◦ Factor structure will be estimated by confirmatory factor analysis (CFA).◦ Agreements between:▪ Reported concern (EWQ) and DBED concluded concern (EWQ), respectively, and mental health (SDQ): correlations (Pearson’s and Spearman), Cohen’s (weighted) Kappa, CFA: uni-, bi-, and tri-factor models representing different sources of information (parent 1, parent 2, teacher. Latent difference score (LDS) models will also be explored for common levels and differences within and between families.Parent’s and teacher’s mental health report (SDQ): correlations (Pearson’s and Spearman), CFA, including method factors, LDS models.Parents’ and teacher’s possible worries for the child: Cross table with chi-quadrat test, Cohen’s weighted Kappa, CFA, and LDS models.▪ Change from reported (EWQ) to concluded concern (EWQ) during the parent-teacher conference: cross table with chi-quadrat test, Cohen’s weighted Kappa, CFA/LDS models.▪ Satisfaction with DBED:Initial: distribution of scores and mean values of each item. Mean value of total score.Follow-up: repeated measures of mean values of each item and total scores and LGC models.▪ Predictors of mental health change, parent concern, teacher concern, parent satisfaction, parental stress: LGC models with predictors (conditional LGC models).Statistical principles◦ Level of statistical significance: We will use the threshold of *p* = 0.05 for the main analysis. However, the threshold perspective has been debated, and there is considerable literature claiming another perspective as a relevant alternative. This implies the use of exact p-values as a degree of certainty of the generalization from sample to population. In the exploratory part of the project, this practice will be used. In addition, we will calculate effect sizes to evaluate the results beyond statistical significance.◦ Adjustment for multiplicity: Detailed power analysis (Monte Carlo analysis) was used to decide sample size for satisfactory power. Adjustment is irrelevant for this analysis. Regarding other statistical analyses, analyses may introduce risk for Type 1 errors when testing family-wise tests. When testing specific hypotheses (see above), no adjustment should be necessary. When exploring differences and relations not pre-specified in hypotheses (family wise tests), Bonferroni corrections will be used.◦ Confidence intervals to be reported: 95%◦ Methods used for assumptions to be checked for statistical methods: Residuals will be saved and checked for normality and homoscedasticity. Relations will be plotted and linearity in relations evaluated.◦ Details of alternative methods to be used if distributional assumptions do not hold: Bootstrapping will be used if normality does not hold. However, larger samples are robust for such deviations.If survival models (Cox and non-proportional parametric hazard models based on Weibull distribution), the proportional assumption will be tested. In addition, covariates will also be tested as time-dependent covariates to explore whether they relate to events differently over time.

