### Trial design {8}

The study design is a cluster randomised open trial, where 20 kindergartens will be randomised to either DBED intervention (*n* = 10) or control groups (*n* = 10). In the control group, parent-teacher appraisals are performed in the traditional way (treatment as usual; TAU). Children’s mental health, as measured by SDQ scores, will be assessed by both parent- and teacher-report biannually through the last 3 years in kindergarten and for the first 2 years in school. Our analyses will examine DBED’s possible superiority to TAU. Similar analyses will be performed as to DBED’s impact on activation of interventions for mental health concerns and parental stress.

The number of components involved, the wide variety of behaviours targeted, expertise and skills required by those delivering the intervention, and the permitted level of flexibility of the intervention confirm that the PRO-DIALOG project is complex intervention research [11]. Hence, in addition to the core trial design, we will use a mixed-method approach to the process evaluation, including both quantitative and qualitative methods. A logic model of the project can be found in Additional file 1.

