### Sample size {14}

The participating children are expected to represent the general population and are not a clinical sample with a presumed high level of mental symptoms. Hence, even if DBED will have a promoting effect on mental health among the children, the difference between the intervention and the control group will probably be small. In the absence of other similar studies, we chose a difference of 0.8 in SDQ Total Difficulties Scale score based on discussions in the project group. Then, we powered the study to be able to detect such a difference between the implementation and the control group. Mplus was used for Monte Carlo simulations assuming the participation of 20 kindergarten (clusters) with ten participating subjects within each cluster and a baseline SDQ mean 5.5 (English norm data: 5.7) SD = 5.5 (σ^2^_within_ = 30.25). The group differences were represented with a predictor of the slope factor in a latent growth curve model. The model assumed normative stability in the controls (mean change = 0.0) and a reduction of −0.8 in the intervention group during the total period. Group sizes were set to be equal. Some between-cluster variation was specified in the intercept factor (σ^2^_between_ = 2.0) to give expected ICC = 0.10 in the six outcome variables over time. The attrition was assumed to be up to 25%. The number of replications was 1000. To achieve the difference of 0.8 with a sample size of *n* = 100 in each group, the statistical power for the testing of group difference was found to be 95%.

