## Discussion

In societies with high preschool uptake, such as Norway, kindergartens have great potential for mental health promotion in young children. Targeted interventions in preschools, where children may require additional support, have been proven to deliver far greater societal returns compared to interventions introduced later in life [4]. We believe that the PRO-DIALOG project holds the potential to generate such an impact and have both short-term and long-term benefits for individuals and society.

To our knowledge, this is the first trial to investigate a systematic parent-teacher conference in kindergartens aiming to promote child mental health. To avoid contamination of the intervention on control cases, a block randomized design was regarded as appropriate. With this design, all teachers to the children of the eligible birth cohorts in the intervention kindergarten receive training in DBED. Likewise, all the eligible parents are informed and invited to participate.

Despite the RCT design, assuming equality between the intervention and control group might be optimistic. However, adjusting for differences by both a multi-variable and multi-level approach will mitigate such a bias.

As far as we know, there is no convention for what a significant difference in mental health level (SDQ Total difficulties score after 3 years) is in a community-based population exposed to a secondary preventive measure. Hence, our power estimation is based on a somewhat uncertain assumption. The recruitment of parents will go on until the minimum number of participants is reached; however, it will not stop before all invited parents have been given the opportunity to consent to participation. So, the number of participants will probably exceed 100 + 100.

Along with the core trial, aspects beyond the long-term outcome of child mental health are addressed, such as screening properties and social validity of this novel method. For further studies of DBED, these process data will be of great interest.

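### Kindergartens are randomised and the treatment effect is a difference in slope, but the primary models name no kindergarten-level variation in slope and do not say which of them gives the primary p-value

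*Protocol article*

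**What the plan says.** Trial design {8}: "The study design is a cluster randomised open trial, where 20 kindergartens will be randomised", ten to each arm.

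Sample size {14}: the simulation was run "assuming the participation of 20 kindergarten (clusters) with ten participating subjects within each cluster". Group enters as a predictor of the slope factor, with this effect: "The model assumed normative stability in the controls (mean change = 0.0) and a reduction of −0.8 in the intervention group during the total period". On clustering: "Some between-cluster variation was specified in the intercept factor", with a between-kindergarten variance of 2.0. No between-kindergarten variance is given for the slope.

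Statistical methods {20a}, primary outcome: "Both random intercept fixed slope and random intercept random slope will be analyzed, meaning models with no variance in change (slope"), the alternative being a slope that differs from child to child. An unstructured intercept and slope matrix is tested next, then non-linear shapes, predictors and within-level residual structures. The section treats latent growth curves and multilevel models as equivalent when specified alike. It sets a threshold of 0.05 and 95% confidence intervals, and does not say which of the listed models supplies them.

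Discussion: on baseline differences between the arms, "adjusting for differences by both a multi-variable and multi-level approach will mitigate such a bias".

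**The concern.** In a cluster-randomised trial, the error term for a treatment effect has to include how much the quantity being compared varies between clusters. Here that quantity is change over time. If children in some kindergartens improve or worsen together for reasons unrelated to DBED, the ten kindergarten slopes per arm scatter more than the child-level slopes alone imply. A model with no slope variance, or with slope variance between children only, does not see this scatter.

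A kindergarten intercept does not help. It shifts all waves of a kindergarten equally, so it drops out when change is computed.

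The fixed-slope model adds a second problem: it assumes that all children in an arm change at the same rate, which makes the standard error of the slope difference too small if they do not. With both models to be analysed and no rule for choosing, two different p-values are available for the one primary test. At stake are its 5% error rate and the coverage of its 95% interval.

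**Working it through.** **The plan's own figures.** The stated 95% power cannot be reproduced from the article, because the slope test needs a residual variance and a child slope variance that are not given. It is taken as stated below. The stated ICC of 0.10 concerns SDQ level, not change, so it supplies no value for the slope.

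**Inputs from the article.** 20 kindergartens, 10 per arm; m = 10 children per kindergarten; attrition up to 25%, so m = 7.5 at worst; six waves to the primary endpoint; threshold 0.05, taken as two-sided.

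**Assumed, because the article gives no value.** The slope ICC (the share of the variance of children's estimated change that lies between kindergartens), shown from 0 to 0.10. For step 3, the child slope SD and the residual variance.

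**1. Which variances enter.** Write each child's score as kindergarten intercept + child intercept + (kindergarten slope + child slope) × time + residual. The estimated change of a child contains both slopes and the residual, but neither intercept. The planned kindergarten variance of 2.0 therefore contributes nothing to the error of the slope difference.

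**2. Slope variance at child level only.** The true variance of the slope difference exceeds the model's by DE = 1 + (m − 1) × ICC. The type I error of a nominal 5% test is 2 × [1 − Φ(1.96/√DE)].

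| Slope ICC | DE (m = 10) | SE too small by | Type I error, m = 10 | Type I error, m = 7.5 |
|---|---|---|---|---|
| 0 | 1.00 | 1.00 | 5.0% | 5.0% |
| 0.02 | 1.18 | 1.09 | 7.1% | 6.5% |
| 0.05 | 1.45 | 1.20 | 10.4% | 8.9% |
| 0.10 | 1.90 | 1.38 | 15.5% | 12.7% |

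For example, at 0.05: √1.45 = 1.204, 1.96/1.204 = 1.628, two-sided p = 0.104. A simulation of balanced, complete data (20,000 replicates) agrees: 5.1–5.3% at ICC 0, then about 7%, 10.5% and 16%. In the same simulation a kindergarten-level t test on 18 df held 4.8–5.1% throughout.

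**3. Fixed slope, no kindergarten effect at all.** Scale the six waves from 0 to 1, so Sxx = 0.7. The true variance of a child's slope is V = slope variance + residual/0.7. The fixed-slope model uses a pooled residual of (4 × residual + 0.7 × V)/5, divided by 0.7. Assume a child slope SD of 2 to 3 points over the period and stability of 0.7 to 0.9, so residual variance = (1 − stability) × 30.25.

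- Mildest case (SD 2, stability 0.7): residual 9.075; V = 4 + 12.964 = 16.964; pooled residual 9.635; model variance 13.764; ratio 1.232; type I error 7.7%.
- Strongest case (SD 3, stability 0.9): residual 3.025; V = 9 + 4.321 = 13.321; pooled residual 4.285; model variance 6.121; ratio 2.176; type I error 18.4%.

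**4. Effect on power.** If 95% is the power of a child-level z test, the standardised effect is 1.960 + 1.645 = 3.605. Dividing by √DE and testing on t with 18 df (critical value 2.10) gives about 93%, 88%, 81% and 70% at slope ICC 0, 0.02, 0.05 and 0.10 with m = 10.

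**The case against.** **The inflation depends on an unknown.** The slope ICC is nowhere in the article, and at zero the child-level random-slope model keeps its size. This stands, and the figures are conditional on it. However, the article expects kindergartens to differ in SDQ level, and both the intervention and the teacher-reported SDQ come from each kindergarten's own staff. Exactly zero variation in change is therefore a strong assumption to build in.

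**Clustering is not ignored.** A reader might infer that the Discussion holds the only multilevel statement. That is not so: the sample-size section has a between-kindergarten variance, and the methods section refers to multilevel models and within-level residuals. A kindergarten slope is not excluded. Yet where the slope options are spelled out, the only slope variation named is between children, below the level of randomisation.

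**The fixed-slope model may be only a first step.** The sequence reads like nested model building. In the scenarios of step 3, an approximate F test at 5% would detect the child slope variance with about 78% power in the mildest case, 96% in the next and over 99% in the rest. So 8–18% would arise only if a fixed-slope model were reported although children differ in change. What stands is that no selection rule is given.

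**Large-sample robustness.** A reader might take "Bootstrapping will be used if normality does not hold. However, larger samples are robust for such deviations" as a claim that 20 clusters are enough. In context it concerns departures from normality and makes no claim about the number of clusters.

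**Degrees of freedom and the bootstrap unit** are commonly left to the analysis plan. Their absence is not a defect here, and they appear only in the remedy. The cost of a z reference once kindergarten slopes are modelled should not be overstated either. Simulated maximum-likelihood z tests gave about 4.6% at ICC 0, rising to about 7.9% at 0.10, so 7.9% is an upper case.

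**Conclusion.** The point holds in conditional form. As written, the primary models place slope variation at child level or nowhere, while treatment is assigned to kindergartens and its effect is a slope difference. The article also leaves open which model gives the primary p-value and interval. With 10 children per kindergarten, the resulting type I error is about 7%, 10% and 16% at an assumed slope ICC of 0.02, 0.05 and 0.10, and 5% at zero. With 7.5 children it is about 6.5%, 9% and 13%. These figures rest on equal cluster sizes, a two-sided z test and a final model without a kindergarten slope. The fixed-slope model is additionally too liberal whenever children differ in change.

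It would go too far to say that the primary p-value is too optimistic as a matter of fact. The article gives no slope ICC and does not rule out a kindergarten slope. The point is nonetheless more than missing detail, because the stated random effects sit at the wrong level for the test they support.

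**What to change.** Name one primary model: group by time, with random intercept and random slope for both child and kindergarten. Test the group effect on change against a reference suited to 20 clusters, for example t with about 18 df (20 kindergartens less 2 arms), or a re-randomisation test that permutes kindergartens within organisation, as they were allocated. State that this model alone gives the primary p-value and 95% confidence interval. Keep the fixed-slope model as a model-building or sensitivity step. If bootstrapping is used, resample kindergartens. Rerun the power simulation with a range of kindergarten slope variances.

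The change needs only wording and a rerun of the simulation. The price is a wider interval: compared with a child-level z interval, by a factor of √DE × 2.10/1.96, which is about 1.07, 1.16, 1.29 and 1.48 at slope ICC 0, 0.02, 0.05 and 0.10. Power falls accordingly. The choice should be fixed before outcome data are seen by arm.

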**Methods:**

Ten kindergartens will be randomly selected to implement DBED, while ten will act as controls, offering ordinary parent-teacher conferences. Parents of at least 100 + 100 children will be recruited. The primary outcome will be children’s mental health in the intervention group as assessed by the Strengths and Difficulties Questionnaire (SDQ), during the 5-year follow-up, compared to the control group. Secondary outcomes will be (i) the effect of DBED on parental stress as measured by the Parental Stress Scale (PSS) and (ii) time to activation of support, as measured by the duration from the first parent-teacher conference to activation of any support, comparing the two groups. We will also assess (iii) socio-demographic predictors for mental health development, parent and teacher concern for the child, parental stress, and parent satisfaction with DBED, (iv) screening properties of DBED compared to SDQ, and (v) social validity of DBED as measured by user-satisfaction questionnaires and interviews with both parents and teachers.

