### Intervention description {11a}

#### Intervention

DBED [10] is a 3-step method (Fig. 1) starting with both parents and kindergarten teachers completing the Early Worry Questionnaire (EWQ) (Step 1) as a preparation for the biannual parent-teacher conference. The EWQ contains 37 questions that systematically map possible concerns for the individual child’s wellbeing and development. When a concern is stated, the respondents are asked to suggest possible causes in an open-ended follow-up question. Step 2 is the parent-teacher conference where they compare their answers from the EWQ and discuss whether there is a reason for concern or not. In case of consensus of concern, a discussion of possible further actions should follow (Step 3), such as closer observation of the child, simple educational interventions (e.g., playgroup), or referral to more specific external assessment or services. During feasibility testing (*N* = 153) of the method, DBED was well accepted by parents and teachers [10]. Preparation before parent-teacher conferences by completing the EWQ facilitated a more active involvement of the parents in the dialogue. They also more often presented previously unspoken concerns for their child [10].

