### Outcomes {12}

Primary outcome:

Effect of DBED on mental health measured as the difference between intervention group and control group in Total difficulties score of SDQ. Measurement scores will be recorded every sixth month during the entire 5-year project period (i.e., child-age 3 to 8 years) as repeated measures. SDQ sub-scores and two impact scores (difficulties in general and impact on four areas of daily functioning) will be analyzed. The primary endpoint will be during the last 3 months in kindergarten before the child starts school, giving total change over six time points of measurements. The secondary endpoint will be during the last 3 months in the second school year (10 time points of measurements).

Secondary outcomes:

Effect of DBED on time to initiated locally available supportive action analyzed as the difference in time (months) from inclusion to activation of such actions between the intervention group and control group as mean time (months) from inclusion to activation of such actions. This outcome will indicate if DBED may lead to earlier supportive actions for children.Effect of DBED on parental stress analyzed as the difference in total scores of the PSS between the intervention group and the control group [12]. Measurements will be recorded every sixth month during the project period. This outcome will indicate if DBED may lead to less or more parental stress and more or less self-confident parents.

Process outcomes:

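### Time to supportive action is defined as a mean and assigned the growth-curve method of the primary outcome; children with no action are not provided for, and survival models appear only in an unattached conditional sentence.

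*Protocol article*

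**What the plan says.** The section Outcomes {12} lists time to locally available supportive action as a secondary outcome, compared between arms "as mean time (months) from inclusion to activation of such actions".

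The section Statistical methods for primary and secondary outcomes {20a} gives the method: differences between the arms "in parental stress and time to initiated locally available supportive action, respectively, will be analyzed in a similar way to the primary outcome". For the primary outcome, differences in trajectories "will be estimated by Latent growth curve (LGC) models (gives equal results as linear mixed/multilevel models, given similar parameter specification", with random intercepts and slopes over the half-yearly scores.

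Later in the same section, among the assumption checks, stands an incomplete sentence: "If survival models (Cox and non-proportional parametric hazard models based on Weibull distribution), the proportional assumption will be tested". It names no outcome.

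The abstract uses a different time origin. There the outcome is described "as measured by the duration from the first parent-teacher conference to activation of any support", whereas Outcomes {12} counts from inclusion.

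The participant timeline {13} shows actions recorded at the six kindergarten rounds, with old and new actions kept apart, and not in the two school years. Section {20c} prescribes intention to treat and multiple imputation. It does not mention censoring.

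**The concern.** A growth curve needs a repeated response. Time to a first action is one number per child, so there is no slope to estimate. A child with no action by the last kindergarten round has no observed time at all; it is known only that the time exceeds follow-up. The protocol does not say how such a child enters the mean.

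The simplest reading, averaging over children who had an action, compares groups selected by something that happens after randomisation. It also discards the main way in which earlier support would show itself, namely more children reaching an action within follow-up. The outcome is meant to show whether DBED brings support forward, so a metric that barely responds to that effect could yield a null result when the effect is real.

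With two incompatible methods in one section, the choice between them is also left open until after data are seen.

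**Working it through.** **No figure to reproduce.** The protocol gives no action rate, effect size or power for this outcome. What follows shows the consequence under stated assumptions.

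**Inputs from the protocol:** 100 children per arm (Sample size {14}); three kindergarten years with half-yearly recording of actions (timeline {13}); threshold 0.05 ({20a}), taken as two-sided.

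**Assumptions:** constant hazards; horizon H = 36 months; share F of control children with an action by 36 months between 10% and 50%; hazard ratio (HR) 2; no dropout; no clustering.

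**Formulas**

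- Hazard: λ = −ln(1 − F)/H. In the DBED arm the hazard is 2λ, so the share with an action is 1 − (1 − F)².
- Mean time among children with an action: 1/λ − H(1 − F)/F.
- Restricted mean over all children: F/λ.
- Each arm uses its own λ and F.

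**Worked case, F = 20%**

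- Control: λ = 0.22314/36 = 0.006198, so 1/λ = 161.3 months. Mean among children with an action = 161.3 − 36 × 0.80/0.20 = 17.3. Restricted mean = 0.20 × 161.3 = 32.3.
- DBED: share with an action 1 − 0.80² = 36%, 1/λ = 80.7. Mean among children with an action = 80.7 − 36 × 0.64/0.36 = 16.7. Restricted mean = 0.36 × 80.7 = 29.0.
- Differences: about 0.7 month and 3.2 months.
- The unrestricted means, 161 and 81 months, lie far beyond follow-up and cannot be observed.

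**Range at HR 2**

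| Action by 36 months, control / DBED | Mean among children with an action (months) | Difference | Restricted mean, all children (months) | Difference | Power: t-test on that mean | Power: log-rank, all children |
|---|---|---|---|---|---|---|
| 10% / 19% | 17.7 v 17.4 | 0.3 | 34.2 v 32.5 | 1.7 | 5% | 42% |
| 20% / 36% | 17.3 v 16.7 | 0.7 | 32.3 v 29.0 | 3.2 | 7% | 74% |
| 30% / 51% | 16.9 v 15.9 | 1.0 | 30.3 v 25.7 | 4.5 | 8% | 85% |
| 50% / 75% | 15.9 v 14.0 | 2.0 | 26.0 v 19.5 | 6.5 | 18% | 97% |

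Power comes from 1,000 simulated trials per row, with event times rounded up to the next six-month round. Schoenfeld's formula gives 46%, 74%, 88% and 97% for the log-rank column. At F = 20% and HR 1.5 the two powers are 5% and 29%. In the most favourable case run, F = 50% and HR 3, they are 58% and 100%. Clustering would lower all of these.

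**Horizon.** The timeline places consent at month 3 of year 1 and the last round at months 10–12 of year 3, which is 24 + 10 − 3 = 31 to 24 + 12 − 3 = 33 months. If F refers to the end of that period, every time in the table scales by 31/36 to 33/36, which is 8% to 14% smaller. The ratio between the two differences does not change.

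**Time origin.** Consent at month 3 and first conference at months 4–6 puts the two origins about 1 to 3 months apart. A child whose conference never takes place has an inclusion date but no conference date.

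**The case against.** The best defence is that the authors did have survival analysis in mind. Section {20a} names Cox and Weibull models, a proportionality check and time-dependent covariates, and time to action is the only listed outcome with an event. This stands to the extent that the protocol cannot be read as fixing a growth curve and nothing else. It does not remove the fault, because the sentence is conditional, names no outcome and conflicts with the explicit assignment of the primary outcome's method.

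Second, Outcomes {12} does not say that the mean is confined to children with an action. That is right: the calculation tests one reading. No other reading is described, however, and an unrestricted mean over all children cannot be observed. An event that has not yet happened is also not a missing value in the ordinary sense, so the general reference to multiple imputation does not settle how these children count.

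Third, a reader might infer that most children will have no action. The documents do not say so. The children "are expected to represent the general population and are not a clinical sample with a presumed high level of mental symptoms", which makes a low rate plausible, and actions in the DBED arm follow agreed concern: "In case of consensus of concern, a discussion of possible further actions should follow". But those actions include low-threshold steps, "such as closer observation of the child, simple educational interventions (e.g., playgroup), or referral to more specific external assessment or services", and there are six rounds, so the rate could be substantial. The point needs only that some children have no action, and the loss is still clear at a 50% control rate.

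Fourth, the two time origins lie close together for children who attend, and the outcome definition itself already uses inclusion. That part is a small correction to the abstract.

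Finally, model form can be left to an analysis plan, which may exist but is not shown. A conflict in the protocol's own text is a different matter.

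**Conclusion.** The point holds as an inconsistency and a poor choice of metric and method for a secondary outcome. The protocol states a mean time and a growth-curve approach, neither of which suits a censored single time per child, and it mentions survival models without attaching them to anything.

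At a hazard ratio of 2 and assumed control action rates of 10% to 50%, a mean among children with an action shows a difference of 0.3 to 2.0 months, where the restricted mean over all children shows 1.7 to 6.5. These are different estimands. The comparison shows how much of an effect on activation the first one misses. The rates, the hazard ratio and the constant hazards are assumptions, and the figures apply to that one reading of the mean.

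Three stronger conclusions are not supported:

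- **That the outcome cannot be validly estimated.** The planned half-yearly action reports would support a proper survival analysis; the fault lies in the metric and method as written.
- **That this is a key secondary outcome.** The protocol lists two secondary outcomes and does not rank them.
- **That the comparison would change sign.** Every effect calculated here keeps its direction, and nothing in the documents indicates a pattern that would reverse it.

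The primary outcome and the sample size are unaffected.

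**What to change.** In Outcomes {12} and Statistical methods {20a}, replace the plain-mean wording and the reference to the primary outcome's method with one time-to-event analysis of all children as randomised:

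- Time zero is inclusion in both arms; align the abstract with this.
- The event is the first new action. The timeline already separates new from old actions.
- Children without an action are censored at their last action report.
- Kindergarten clustering and the organisation within which randomisation took place are accounted for.
- If actions are known only by half-yearly round, use a discrete-time or interval-censored model. The action questionnaire is in an additional file that is not shown, so whether start dates are recorded has to be checked first.
- Report the hazard ratio, the cumulative incidence by arm and the difference in restricted mean time. The last of these keeps a result in months, as the outcome definition intends.

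The conditional sentence on Cox and Weibull models should then be attached to this outcome or removed. The cost is a wording change in the protocol and analysis plan, best made before outcome data are analysed. It uses reports already planned and needs no additional children.
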